### Trial design and schedule

#### Phase I trial: dose escalation to determine MTD

The purpose of the phase I trial is to determine the MTD of salvage raster-scanning CIRT with concurrent cisplatin-based chemotherapy for locally recurrent NPC. Patients who meet the inclusion criteria will be treated with chemotherapy and this dose-escalating CIRT scheme, and acute and subacute toxicity during the treatments and within 4 months after CIRT will be observed.

The study includes 6 increasing dose regimens starting at 52.5 GyE (2.5 GyE × 19 fractions) up to 65 GyE (2.5 GyE × 26 fractions) using the TITE-CRM design of phase I trials, with the starting dose/fraction at 55 GyE delivered daily in 22 fractions. The trial will be concluded at 65 GyE if the MTD is not reached, and 65 GyE/26 fractions will be the recommended dose/fractions for the phase II trial. The probability of dose limiting toxicity (pDLT) for each dose level is estimated based on published data for re-irradiation with CIRT to the head and neck area (Table 1).

**Table 1 Tab1:** Treatment schedule (CIRT plus concurrent chemotherapy) for dose escalation in patients with locally recurrent nasopharyngeal carcinoma (NPC)

Dose level	Dose and fractionation	Total dose (GyE)	pDLT (%)	BED2 (GyE)	BED9 (GyE)
1	2.5 GyE × 21 fractions	52.5	<5	118.1	67.1
*2*	*2.5 GyE* *×* *22 fractions (starting dose)*	*55*	*10*	*123.8*	*70.3*
3	2.5 GyE × 23 fractions	57.5	20	129.4	73.5
4	2.5 GyE × 24 fractions	60	30	135.0	76.7
5	2.5 GyE × 25 fractions	62.5	40	140.6	79.9
6	2.5 GyE × 26 fractions	65	50	146.3	83.1

The starting dose of the trial is at 2.5 GyE *×* 22 (in italics)

*CIRT* carbon-ion radiotherapy, *GyE* gray equivalent, *pDLT* probability of dose-limiting toxicities, *BED* biological effective dose, *BED2* cumulative BED with an α/β ratio of 2, *BED9* cumulative BED with an α/β ratio of 9

A maximum of 25 patients for the 6 dose levels (starting at 55 GyE) is projected for phase I trial (i.e., the dose-escalating stage of the trial). Based on our clinical load, we expect to recruit an average of 1 patient per week. We expect that the phase I trial will be completed in 24 months, since the first patient at each dose level will be followed up for 4 months before dose escalation.

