### Statistics (see footnote 1)

#### Phase I trial

The primary objective is to determine the CIRT dose when used with concurrent cisplatin-based chemotherapy, which is associated with a DLT in less than 25% of previously treated NPC patients with a local recurrence. DLT is defined as any grade 4 toxicity (CTCAE v. 4.03) that is possibly, probably, or definitely associated with CIRT that occurred within 6 months after completion of re-irradiation [24]. Treatment-induced adverse effects also include deterioration in Eastern Cooperative Oncology Group performance status to ≥3 that develops during the same follow-up period. The secondary objectives are OS and local progression-free survival. The MTD of CIRT for re-irradiation used with concurrent cisplatin-based chemotherapy will be determined at the end of phase I trial.

Dose levels of CIRT will be assigned based on the TITE-CRM algorithm [21]. During the trial, pDLT will be continually updated, using data from all enrolled patients and their updated outcomes obtained through follow-up visits. Patients with partial follow-up at a time of new enrollment (i.e., <4 months) will be weighted by the proportion of the follow-up time completed. Newly enrolled patients will be assigned to the dose that is estimated to have a pDLT closest to but not higher than 0.25.

Four patients will be entered to the starting dose level. Dose escalation is restricted to one level between any 2 patients. Prior to escalation, at least 1 patient must have completed the full course of treatment and the full observation period (6 months) at the previous dose level without a DLT. Six dose levels and their initial estimation of the pDLT are planned within the phase I trial (Table 1). The dose will be increased until DLT is observed or when 65 GyE is reached.

As described above, the phase I trial was designed to accrue up to 25 patients. We estimate that 4 patients will be accrued each month. Patients who complete 90% or more of the planned CIRT dose will be considered evaluable. Patients who complete 90% or more of the planned CIRT dose but become un-evaluable for 6 months will be counted as evaluable in the final analysis and weighted by the proportion of the observation period for which they were evaluable. Replacement of any accrued patient can only be considered if the patient did not complete therapy for reasons other than toxicity.

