At the end of the trial, a simple two-parameter logistic regression model will be used to estimate the pDLT at each dose level. Secondary endpoints are the response of tumor to CIRT, local progression-free survival, OS, and other toxicity and safety data on the studied dose levels. The Kaplan–Meier method will be used to evaluate the OS and local progression-free survival of all patients. SAS v.9.1 software (SAS Institute Inc, Cary, NC, USA) will be used for statistical analyses. The Cox proportional hazards model will be used for multivariate analysis, as the univariate results indicate.

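### Phase I states two escalation rules that conflict as written, and its final logistic model will often have no finite or identifiable slope

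*Protocol article*

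**What the plan says.** The subsection on the phase I trial under Statistics seeks a CIRT dose "which is associated with a DLT in less than 25% of previously treated NPC patients with a local recurrence". Dose levels are assigned by TITE-CRM: "During the trial, pDLT will be continually updated, using data from all enrolled patients", and "Newly enrolled patients will be assigned to the dose that is estimated to have a pDLT closest to but not higher than 0.25". Four patients enter at the starting level, escalation moves one level at a time, and one patient must complete observation without a DLT before each step up. The same paragraph as those restrictions ends: "The dose will be increased until DLT is observed or when 65 GyE is reached". No number or rate of DLTs is attached to that sentence.

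For the end of phase I, the plan is that "a simple two-parameter logistic regression model will be used to estimate the pDLT at each dose level". No fitting method is named.

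Table 1 gives anticipated DLT probabilities of <5%, 10%, 20%, 30%, 40% and 50% for levels 1 to 6, starting at level 2. On size: "A maximum of 25 patients for the 6 dose levels (starting at 55 GyE) is projected for phase I trial".

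The section on dose escalation to determine the MTD describes the range thus: "The study includes 6 increasing dose regimens starting at 52.5 GyE (2.5 GyE × 19 fractions". Table 1 gives 21 fractions for 52.5 GyE, and the Abstract gives 21 to 26 fractions for 52.5 to 65 GyE.

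**The concern.** A model-based design treats a DLT as information. The estimate rises, the next patient may be held or moved down, and escalation resumes if later patients do well. A rule that raises the dose only until a DLT appears has no such return path. Both cannot govern the same trial. Whichever is followed shapes which doses are ever tried, and the phase I result fixes the phase II dose.

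The final analysis raises a related question. A two-parameter logistic curve needs DLTs and non-DLTs to overlap across doses. With at most 25 patients and few DLTs, the overlap may be absent, and a first-DLT stop makes that more likely.

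**Working it through.** **Plan figures.** The plan states no operating characteristic for phase I, so there is none to reproduce. On Table 1, the level closest to but not above 0.25 is level 3 (20%).

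**1. Chance of a literal stop at the starting level.** Inputs: 10% (Table 1) and four patients (Statistics, phase I).

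P(at least one DLT) = 1 − 0.9^4 = 1 − 0.6561 = 0.344.

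**2. Chance of stopping at level 2 or 3.** The number of patients per later level is not stated, so *m* at level 3 is an assumption.

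P = 0.3439 + 0.6561 × (1 − 0.8^m)

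| m at level 3 | P(stop at level 2 or 3) |
|---|---|
| 1 | 0.3439 + 0.6561 × 0.2000 = 0.475 |
| 4 | 0.3439 + 0.6561 × 0.5904 = 0.731 |
| 5 | 0.3439 + 0.6561 × 0.6723 = 0.785 |

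With m = 4 the total splits into 0.344 at level 2 and 0.387 at level 3, so more than half falls at the level that the 0.25 rule selects on Table 1.

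**3. Do the two rules disagree on the same data?** The check uses a one-parameter power-model CRM, p_k = s_k^exp(β) with β ~ N(0, v). The s_k are Table 1's values, with level 1 taken as 4%. Model and prior are assumptions; the document gives neither.

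- 0/4 at level 2 and 1/4 at level 3 (v = 1.34): level 4 is estimated at 0.276. Neither rule goes up.
- Four more patients at level 3 without a DLT (0/4 and 1/8): level 4 is estimated at 0.206. Over v from 0.5 to 2, by plug-in or posterior mean, it is 0.19 to 0.22. The 0.25 rule now allows level 4; the literal sentence has already ended escalation.

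The two rules do not differ at every DLT. With 1/4 at level 2 and v = 1.34, the model puts level 3 at 0.367 and would not escalate then either. The difference is that the model's hold can be reversed.

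**4. Simulated consequence.** 1,500 trials per scenario, weekly accrual, uniform DLT times, four patients per level before escalation, and the CRM above. With Table 1 as the truth, the highest level used stays at level 2 in 34.0% of trials if accrual ends at the first DLT, 33.2% if the first DLT only caps escalation, and 14.8% under TITE-CRM alone.

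**5. The final logistic model.** With logit p = a + b·dose, suppose all DLTs occur at the highest dose used, D, together with some non-DLTs there. Hold a + bD at the observed logit and let b grow. Fitted probabilities at lower doses tend to 0, and the likelihood rises towards a bound it never reaches. This is quasi-complete separation. If only one dose is used, b is not identified at all.

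Share of the same simulated trials with no ordinary maximum-likelihood estimate:

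| Assumed truth | TITE-CRM alone | First DLT caps escalation | Accrual ends at first DLT |
|---|---|---|---|
| Table 1 | 28.8% | 67.1% | 98.4% |
| Lower toxicity, MTD at level 5 | 43.3% | 89.5% | 98.5% |
| Lowest toxicity, MTD at level 6 | 49.5% | 94.7% | 98.2% |

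**6. Level 1 fraction count.** 2.5 × 21 = 52.5, as in Table 1 and the Abstract. 2.5 × 19 = 47.5, which does not match the 52.5 GyE printed beside it.

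**The case against.** The best defence is that the sentence is shorthand for escalating until the MTD is reached. The sections on dose escalation, on phase II treatment at the recommended dose and on dose prescription all speak of the MTD being reached or determined, and the Statistics section says TITE-CRM assigns doses. This reading is plausible and may be what was meant. It does not remove the conflict in the text, because an escalation rule should not have to be inferred.

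Several stronger inferences are tempting, and the documents do not support them:

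- **That the first DLT defines the MTD, or ends accrual.** No section says so.
- **That the phase I objective would be missed.** The objective is a DLT rate below 25%, and on Table 1 levels 2 and 3 both satisfy it. What a literal stop can miss is the level closest to 0.25.
- **That about 73% of trials would stop in the wrong place.** That figure assumes four patients per later level, and most of it is level 3.
- **That level 1 is somewhere given as 47.5 GyE.** It is not. The total is 52.5 GyE throughout, and only one fraction count is discordant.
- **That the escalation sentence causes the logistic problem.** It does so only in part, since the fit fails often under TITE-CRM alone.

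It is also fair to say that the estimator may be specified in a fuller document, and that a penalised or Bayesian fit would avoid separation. The point about the model is therefore conditional on ordinary maximum likelihood.

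**Conclusion.** The conflict between the two rules is in the text and needs no assumption. From document inputs alone, a literal reading ends escalation at the starting level with probability 0.34, at a dose Table 1 rates at 10%. On the assumed CRM, the comparable chance of never going above that level under TITE-CRM alone is about 15%. The stop at level 2 or 3 ranges from 47.5% to 78.5% as the number at level 3 runs from one to five, and should not be read as an error rate.

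The estimation problem is separate. If fitted by ordinary maximum likelihood, the logistic model fails in 28.8% to 49.5% of simulated trials even with the escalation sentence removed. These figures depend on the assumed CRM, prior, cohort size, DLT timing and toxicity scenarios.

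The fraction count is a minor, independent discrepancy. This review takes no view on which escalation rule or fraction number is clinically right.

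**What to change.** 1. Reconcile the phase I Statistics text so that one rule governs escalation, and align the MTD wording in the sections on dose escalation, phase II treatment and dose prescription with it.
2. State that final DLT probabilities are estimated with the weighted TITE-CRM model already used for assignment, or with a penalised or Bayesian logistic fit. Reconciling the rules alone does not secure the logistic fit.
3. Reconcile the level 1 fraction count between the dose-escalation section and Table 1 and the Abstract.

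The cost is protocol wording and the choice of one estimator. No added patients or visits are needed. Because accrual has already started, the changes should be made before further escalation decisions and before the MTD is declared.

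### The end-of-trial two-parameter logistic fit, read as ordinary maximum likelihood, often has no finite solution with 25 patients; it should use a prior or penalty and state that it carries the follow-up weights

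*Protocol article*

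**What the plan says.** All of this comes from the protocol article, mainly Statistics, Phase I trial.

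- **Final model.** At the end of the trial, "a simple two-parameter logistic regression model will be used to estimate the pDLT at each dose level". SAS 9.1 is named, but no estimation method, prior, penalty or procedure.
- **Weights in the final analysis.** Patients who received at least 90% of the planned dose but later become un-evaluable "will be counted as evaluable in the final analysis and weighted by the proportion of the observation period for which they were evaluable".
- **Weights during the trial.** Patients with partial follow-up when a new patient enrols "will be weighted by the proportion of the follow-up time completed".
- **Assignment.** TITE-CRM is used. New patients are "assigned to the dose that is estimated to have a pDLT closest to but not higher than 0.25", four patients enter the starting level, and escalation is one level at a time.
- **Size.** Under Phase I trial: dose escalation to determine MTD: "A maximum of 25 patients for the 6 dose levels (starting at 55 GyE) is projected for phase I trial". No derivation or operating characteristics are given.
- **Prior pDLTs.** "The probability of dose limiting toxicity (pDLT) for each dose level is estimated based on published data". Table 1 gives <5, 10, 20, 30, 40 and 50% for levels 1 to 6.

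**The concern.** A two-parameter logistic curve needs DLTs and non-DLTs to overlap across dose. This design works against overlap: it has few patients, a cap at 0.25 and single-level steps, so the few DLTs tend to sit at the highest level used. Maximum likelihood then has no finite intercept and slope.

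What is at stake is the reported toxicity estimate for each level. In such a data set the lower levels are reported as 0% and any untreated higher level as 100%, with no usable confidence interval. Those figures reflect the estimator, not evidence about the doses. A second, smaller issue is that the sentence naming the model does not mention the weights that the same section requires.

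**Working it through.** **1. Why the fit fails.** Let level j have dose x_j, n_j patients, y_j DLTs and fitted probability p_j. The two score equations are Σ(y_j − n_j p_j) = 0 and Σ x_j(y_j − n_j p_j) = 0. Multiply the first by the top dose x_K and subtract the second: Σ(x_K − x_j)(y_j − n_j p_j) = 0. If every DLT is at level K, then y_j = 0 below it, which leaves Σ_{j<K}(x_K − x_j) n_j p_j = 0. Every term is positive unless p_j = 0, so no finite solution exists. This is quasi-separation. Positive weights on the patients without a DLT do not cure it.

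**2. What is then reported.** Take an illustrative 0/4, 0/4 and 1/4 at 55, 57.5 and 60 GyE. The slope diverges while p at 60 GyE tends to 1/4. The limit is 0%, 0% and 25% at the treated levels, and 100% at the untreated 62.5 and 65 GyE.

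**3. How often.** The article gives no figure to reproduce, so the design was simulated with 400 trials per setting (Monte Carlo standard error at most √(0.5 × 0.5/400) = 2.5 points).

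- From the article: 25 patients, Table 1 as skeleton, four patients at level 2, one-level steps, estimated pDLT not above 0.25, accrual of about one patient per week, and a wait before escalation. The article gives that wait as both 4 and 6 months; both were run, and the two statements must be reconciled.
- Assumed: one-parameter power working model with normal prior variance 1.34, level 1 at 4%, uniform DLT times, about 4.6 weeks of treatment, and accrual held after 1, 3 or 4 patients per level until escalation is allowed.
- A fit was counted as non-finite if there was no DLT, only one level was used, or there was complete or quasi-complete separation.

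Percentage of trials with no finite maximum-likelihood fit (hold after 1 / 3 / 4 patients):

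| True pDLT | 4-month window | 6-month window |
|---|---|---|
| Table 1 | 25.7 / 30.7 / 33.5 | 30.2 / 39.2 / 43.0 |
| Half of Table 1 | 36.5 / 44.0 / 30.7 | 44.8 / 57.0 / 52.5 |
| Steep (1, 2, 5, 15, 35, 60%) | 27.7 / 40.5 / 44.3 | 34.3 / 51.2 / 52.2 |
| Low (1–10%) | 76.5 / 59.7 / 59.0 | 76.2 / 72.0 / 61.0 |
| Very low (1–5%) | 91.2 / 77.7 / 75.0 | 93.2 / 81.0 / 78.7 |
| More toxic (15–70%) | 10.5 / 10.0 / 9.8 | 10.0 / 12.3 / 13.2 |

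Two repeat simulations of the same design gave somewhat lower figures with Table 1 true. One gave 94/400 = 23.5% (4 months) and 115/400 = 28.8% (6 months), holding after three patients. The other gave about 18–35%, and about 39–47% at half of Table 1. Together these support roughly 20–40% under Table 1. A further 4–8% of trials under Table 1 had a finite fit with a slope of zero or below.

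**4. Which failure.** In the 94 and 115 failures above, all 94 and 112 of the 115 were quasi-separation with DLTs only at the highest level used. Complete separation occurred in 0 and 1 of 400 trials.

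**5. Whether the weights matter.** In an invented 25-patient data set with levels coded 0, 1, 2 (55, 57.5, 60 GyE), the unweighted fit has intercept −1.914 and slope 0.413. At 60 GyE the logit is −1.914 + 2 × 0.413 = −1.088, so pDLT = 0.252. With three patients without DLT at 60 GyE weighted 0.5, the logit is −1.972 + 2 × 0.533 = −0.906, so pDLT = 0.288. The estimate crosses further above 0.25 on weighting alone.

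**The case against.** The strongest reply is that the article names a model, not an estimator. A full protocol or SAP may specify a penalty, a prior or a rule for separation, and an article need not. This stands in part: ordinary maximum likelihood is only the natural reading of a model described as simple. But the model itself is a stated choice, and applied literally it fails too often to leave as worded.

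The second reply is that diverging coefficients do not make every pDLT useless. This also stands. Under quasi-separation the top treated level keeps its observed proportion, which is the figure closest to the 25% limit. The damage is to the lower levels, the untreated higher levels and the intervals.

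Third, some low-toxicity failures are trials with no DLT, and the article already says which dose goes forward if the MTD is not reached at 65 GyE. That is fair for those rows. It does not touch the Table 1 row, where no trial in the tabulated runs was without a DLT.

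Four stronger readings are tempting but not supported:

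- **That the weights are dropped.** The section applies them in the final analysis, the model sentence withdraws nothing, and a logistic likelihood can carry weights.
- **That the MTD decision rests on this fit.** No sentence makes it the selection rule; TITE-CRM assigns doses and updates pDLT.
- **That separation is close to certain** because "The dose will be increased until DLT is observed or when 65 GyE is reached". That sentence does not sit easily with assignment by TITE-CRM and needs reconciling with it, but it was not what was simulated.
- **That the rate is far higher because patients accrue weekly without pause.** The article describes following the first patient at each level before escalation and expects 24 months.

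**Conclusion.** The point holds in limited form. Read as ordinary maximum likelihood, the stated final model would have no finite solution in roughly 20–40% of 25-patient trials if Table 1 is right. The share is generally higher if toxicity is lower (at half of Table 1, higher in five of the six tabulated settings) and about 10% if toxicity exceeds Table 1. The percentages depend on the assumed working model, DLT timing and accrual holds, and on which escalation window applies.

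The usual consequence is 0% below the top treated level, the observed rate at that level and 100% above it, without valid intervals. It is a weakness in the reported dose–toxicity estimates; the documents do not show that it would change the recommended dose. On weights, the only fault is that the model sentence does not repeat a requirement already made.

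**What to change.** Replace the model sentence with one stating that the final pDLT will be estimated with the follow-up weights already required for the final analysis, by either:

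- the TITE-CRM posterior used for dose assignment; or
- a two-parameter logistic model with a weakly informative prior or a Firth penalty.

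Report intervals, and limit the estimates to the levels actually treated. With a proper prior or a penalty the estimate is finite in every data set, so the non-finite share falls to 0%.

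The cost is one sentence and minor programming. The estimates will depend on the prior or penalty, so it should be stated in advance.

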#### Phase II trial

The primary objective of the phase II trial is to evaluate the actuarial 2-year OS rate (π) for patients with locally recurrent NPC who receive CIRT plus concurrent cisplatin-based chemotherapy. The 2-year OS rate for patients with locally recurrent rT3 or rT4 NPC range from 40% to 50% after IMXT or proton re-irradiation [5, 7].

This is the first study to address the efficacy of re-irradiation with CIRT plus concurrent cisplatin-based chemotherapy on locally recurrent NPC. We estimate that CIRT will improve 2-year OS rate by 20% to 70%, compared with IMXT or proton therapy. Thus, confirmatory analysis of the primary endpoint assesses the following test problem: H0: π ≤ 0.50 = π0 versus H1: π > 0.70. The same single-stage design will be used for the phase II trial [27]. The null hypothesis is defined by the true OS rate being 50%, and it will be tested against a one-sided alternative. A sample size of 37 patients will be required, and the null hypothesis will be rejected if 23 or more survivors are observed among 37 patients, with a median follow-up of 2 years. This design yields a type I error rate of 0.05 and a power of 0.8 if the true OS rate is 70%.

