#### Phase II trial: treatment at recommended dose to study efficacy

Once the MTD is determined in the phase I trial, this dose will be used as the recommended dose for the phase II trial. If MTD is not reached at 65 GyE, we will use 65 GyE as the recommended dose.

The primary endpoint of the phase II trial is OS after re-irradiation, at a median follow-up of 24 months. To evaluate the OS rate, all patients will be followed up for at least 12 months or until death. We estimate that 1 patient per week will be recruited to the trial, and a total of 40 patients (minus the number of patients treated at the recommended dose in the phase I trial) will be recruited over approximately 9 months. The phase II trial is expected to be completed in 24 months.

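### The phase II success rule of 23 or more survivors among 37 has a type I error of 0.094, not the stated 0.05; the stated error rates belong to a cut-off of 24, and no cut-off is given for the planned 40

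*Protocol article*

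**What the plan says.** The Statistics section of the protocol article, under Phase II trial, sets out a one-sample test of the 2-year overall survival rate π:

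- Hypotheses: "H0: π ≤ 0.50 = π0 versus H1: π > 0.70". The null is a true rate of 50%, and "it will be tested against a one-sided alternative".
- Design: "The same single-stage design will be used for the phase II trial".
- Size: "A sample size of 37 patients will be required".
- Decision rule: "the null hypothesis will be rejected if 23 or more survivors are observed among 37 patients", at a median follow-up of 2 years.
- Claimed properties: "This design yields a type I error rate of 0.05 and a power of 0.8 if the true OS rate is 70" per cent.

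Under Trial design and schedule, the subsection on phase II treatment at the recommended dose gives a different number: "a total of 40 patients (minus the number of patients treated at the recommended dose in the phase I trial) will be recruited". So 40 is the whole phase II cohort, counting phase I patients who were treated at the recommended dose. The article does not relate 40 to 37.

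**The concern.** The sample size, the cut-off, the type I error and the power of a single-stage design are tied together: once the two survival rates, the number of patients and the cut-off are fixed, the error rates follow. Here a cut-off of 23 out of 37 is an observed rate of 62.2%, and it is not obvious that this is far enough above 50% for a one-sided 5% test with so few patients.

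This is the only success criterion that the article states for the primary efficacy endpoint, and it calls the analysis confirmatory. If the cut-off is too low, a result of exactly 23 survivors would be reported as significant at 5% when it is not. If the number analysed is not 37, the article gives no rule at all.

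**Working it through.** **Inputs**, all from the phase II statistics section unless noted: null rate 0.50; rate for power 0.70; one-sided test; single stage; n = 37; reject if survivors X ≥ 23; claimed type I error 0.05 and power 0.8. From the trial design section: phase II total 40.

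**1. Does the sample size reproduce?** The one-sided normal formula is

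n = [(1.645 × √(0.5 × 0.5) + 0.842 × √(0.7 × 0.3)) / (0.70 − 0.50)]² = 36.5, rounded up to 37.

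So n = 37 agrees with the stated 0.05 and 0.8.

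**2. Error rates of the rule as written.** With X binomial (n, π), the type I error is P(X ≥ r | π = 0.50) and the power is P(X ≥ r | π = 0.70).

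| n | Reject if X ≥ | Type I error | Power at 70% |
|---|---|---|---|
| 37 | 23 (as written) | 0.0939 | 0.8870 |
| 37 | 24 | 0.0494 | 0.8071 |
| 37 | 25 | 0.0235 | 0.6983 |

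At 23 neither stated figure is met; at 24 both are. The type I error as written is 0.0939 / 0.05 = 1.9 times the claim.

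**3. Could an approximation give 0.05 at 23?** Under the null the mean is 37 × 0.5 = 18.5 and the standard deviation is √(37 × 0.25) = 3.04.

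- Without continuity correction: z = (23 − 18.5) / 3.04 = 1.48, tail 0.069.
- With continuity correction: z = (22.5 − 18.5) / 3.04 = 1.32, tail 0.094.

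Neither gives 0.05.

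**4. Which design fits all the stated figures?** A search over exact single-stage designs for the smallest n with type I error ≤ 0.05 and power ≥ 0.80 returns n = 37 with cut-off 24. The number of patients, the type I error and the power therefore agree with one another, and the cut-off is the one figure out of line. A rule of "more than 23" may have been written down as 23 or more; that is an inference, and the arithmetic does not depend on it.

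**5. What a result at the boundary would show.** The exact one-sided 95% lower confidence bound for π is 0.473 at 23/37 (62.2%), which does not exclude 50%. At 24/37 (64.9%) it is 0.5005, which just does.

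**6. If 40 patients are analysed.**

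| n | Reject if X ≥ | Type I error | Power at 70% |
|---|---|---|---|
| 40 | 23 (hypothetical carry-over) | 0.2148 | 0.9680 |
| 40 | 25 | 0.0769 | 0.8849 |
| 40 | 26 | 0.0403 | 0.8074 |

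The cut-off that holds 5% at n = 40 is 26. The first row is not a rule in the article; it shows what would happen if the count of 23 were kept while the denominator grew.

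**7. The alternative.** As written, rates above 0.50 and up to 0.70 fall under neither hypothesis. Rejecting with a test calibrated at 0.50 supports π > 0.50; 0.70 is only the rate at which power is evaluated.

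**The case against.** No usual method rescues the cut-off of 23, and the sentence is intact prose that does not depend on the cited design reference. The reasonable objections concern what surrounds it.

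- **37 and 40 may coexist.** Three of 40 (7.5%) could be an allowance for patients who cannot be evaluated, and a condensed article may leave that to the full protocol. This is possible but not stated. What stands is that the relation is unexplained and the only rule is tied to 37, so the point is secondary.
- **The 0.215 is not the trial's rule.** That is right: it is conditional on carrying 23 over to 40, and the size of the error rests on 0.094.
- **The wording of the alternative changes no decision.** That is also right. The same paragraph makes clear that 50% is tested and that power is taken at 70%. It is a wording correction.
- **Exact figures need complete follow-up.** The binomial calculation assumes that 2-year vital status is known for every counted patient, whereas the article fixes a median follow-up of 2 years and a minimum of 12 months, and calls the rate actuarial. This is a fair limit: moving to 24 makes the stated figures agree but does not by itself secure 5% if patients with shorter follow-up are counted as survivors. It is a separate matter and does not explain the mismatch, because the stated 0.05 and 0.8 are reproduced by the same binomial calculation at 24.

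**Conclusion.** The concern holds. The phase II rejection rule is one survivor too low for the error rates claimed for it: type I error 0.094 instead of 0.05, with power 0.887 instead of 0.8. Both claims are met at 24 of 37 (0.049 and 0.807). It must be corrected because it is the primary decision rule and an outcome of exactly 23 survivors would turn on it. The missing cut-off for 40 patients and the wording of the alternative are real but lesser faults.

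The figures assume independent patients with 2-year survival status known for all who are counted, a one-sided test, and the null and alternative rates given in the article.

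**What to change.** - In the phase II statistics section, change the rule to: reject the null hypothesis if 24 or more of 37 patients survive to 2 years (exact one-sided type I error 0.049, power 0.807 at 70%).
- State one analysed number in both the trial design section and the statistics section. If it is 37, say what the other three of the 40 are for. If all 40 are analysed, use 26 or more of 40 (type I error 0.040, power 0.807).
- Write the alternative as π > 0.50, with power evaluated at π = 0.70.

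The cost is wording only: no patients are added. One more survivor is needed for success at n = 37, and power falls from the 0.887 of the rule as printed to 0.807, which is still the 0.8 that the article promises. The change should be made and dated before the 2-year outcomes are known.
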